### Outcomes

#### Primary outcome

The primary variable is visual acuity. Visual acuity is measured in units of 0.025 (which equates to one letter). Improvement in visual acuity is measured as an increase of 0.025 LogMAR units.

The primary endpoint is the change from baseline to the end of treatment (6 weeks) in visual acuity.

The secondary endpoints are:

• Change in visual acuity from baseline to the end of the follow-up period (week 10)

• Change in visual acuity from baseline to week 3

• Proportion of patients showing a clinically important change in visual acuity (a change of 0.125 LogMAR units or more) at weeks 3, 6 and 10

• Proportion of change in visual acuity [9] at weeks 3, 6 and 10

• Change in binocular functions from baseline to week 6/week 10

• Proportion of patients reporting outcomes in each item of the patient satisfaction questionnaire

• Percentage compliance with treatment

• Proportion and type of adverse event

Proportion of change is measured as follows:

$$\mathrm{Proportion}\;\mathrm{of}\;\mathrm{change}=VA_{\mathrm{as}}-VA_{\mathrm{ae}}/VA_{\mathrm{as}}-VA_{\mathrm{fe}}$$

VA_as_ is vision of amblyopic eye at baseline, VA_ae_ is vision of amblyopic eye at the ‘end of treatment’ and VA_fe_ is the vision of the non-amblyopic eye at the’ end of treatment’ [9]. ‘End of treatment’ is the time point the change is being measured up to, that is, weeks 3, 6 and 10.

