## Methods/design

### Objectives of the study

The primary objective of the study is to investigate whether there is any difference in visual acuity in patients treated with I-BiT™ *versus* non-I-BiT™ and also if there is any difference between the two treatment stimuli (interactive game *versus* DVD). Therefore two comparisons will be made: differentiation of the type of I-BiT™ treatment and differentiation of I-BiT™ from non-I-BiT™.

Secondary objectives include examining visual acuity at additional time points (mid-treatment and 4 weeks after treatment has stopped), investigating the proportion of patients showing a response to treatment (a change from baseline of 0.125 or more [7]), the proportion of change in visual acuity, the change in binocular function, the acceptability of the treatment to the patient, compliance with treatment, and the safety profile of the treatment.

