### Week 3 (mid-treatment)

Uniocular assessment of visual acuity with a LogMAR test (aided with glasses if applicable) after third treatment.

If at this visit, visual acuity in the amblyopic eye has regressed by 0.1 LogMAR units or more, then the participants should be withdrawn from the study.

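### The outcome section words improvement as an increase in LogMAR units and gives the 0.125 responder rule no direction; benefit is plainly intended, but the text does not fix it

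*Protocol article*

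**What the plan says.** All of this is in the protocol article.

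- **Primary outcome, scale and direction.** "Visual acuity is measured in units of 0.025 (which equates to one letter"). The next sentence gives the direction: "Improvement in visual acuity is measured as an increase of 0.025 LogMAR units".
- **Primary outcome, primary endpoint.** "The primary endpoint is the change from baseline to the end of treatment (6 weeks) in visual acuity". No order of subtraction is given.
- **Primary outcome, secondary endpoints.** "Proportion of patients showing a clinically important change in visual acuity (a change of 0.125 LogMAR units or more) at weeks 3, 6 and 10". No sign is given.
- **Objectives of the study.** The same endpoint appears as "investigating the proportion of patients showing a response to treatment (a change from baseline of 0.125 or more [7"]). Again there is no sign, but it is called a response.
- **Week 3 (mid-treatment).** A child is to be withdrawn if "visual acuity in the amblyopic eye has regressed by 0.1 LogMAR units or more". Here the direction is given by a word and the size by a number.

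**The concern.** LogMAR is the logarithm of the minimum angle of resolution. A larger value means that a larger angle is needed to resolve the target, so vision is worse and improvement is a fall in the score. The one sentence in the outcome section that attaches a direction to the scale attaches the opposite one, and the responder rule attaches none.

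A programmer working from this text could code the responder rule in three ways: a fall of at least 0.125 (evidently intended), a move of at least 0.125 either way, or a rise of at least 0.125 (the rule joined to the stated direction). The second dilutes the contrast between arms with children who lost vision. The third counts only those children. For the continuous primary endpoint, the risk is a difference reported with the wrong sign, and hence the wrong arm called better.

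**Working it through.** **1. Does any other text settle the direction?**

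The pilot results in the Background, the week 3 rule and the sample-size difference are all magnitudes. The proportion-of-change formula, read with its evident brackets as (baseline − follow-up) / (baseline − fellow eye), does not settle it either. With invented values 0.6, 0.4 and 0.0 it gives 0.2/0.6 = 0.33. With the scale reversed (−0.6, −0.4, 0.0) it gives −0.2/−0.6 = 0.33. It is positive for improvement whichever way the scale runs. The article describes no reversed scoring.

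**2. Does the sample size depend on the sign?**

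Inputs from Sample size: SD 0.25, difference 0.2, two-sided 5%, 80% power.

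n per arm = 2 × (1.960 + 0.842)² × 0.25² / 0.2² = 24.5, so 25, and 3 × 25 = 75. The plan's figures reproduce. Power at 25 per arm is 80.7% for a difference of +0.2 and for −0.2 (79.1% with the t distribution). Nothing here depends on direction. Reversing the sign of the change likewise reverses the ANCOVA estimate and leaves its two-sided p-value as it was.

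**3. What does the missing direction do to the responder endpoint?**

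The threshold is 0.125/0.025 = 5 letters. Let the gain (baseline minus follow-up) be normal with mean m and SD s:

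- improved by ≥ 0.125: Φ((m − 0.125)/s)
- worsened by ≥ 0.125: 1 − Φ((m + 0.125)/s)
- either direction: the sum

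Inputs: active m = 0.18 (pilot mean, Background); s = 0.25 (Sample size, taken here as the SD of change) or 0.143 (pilot SD, Background). A control mean of 0 is an assumption, because the article gives none.

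Example, active arm with s = 0.25: Φ(0.055/0.25) = Φ(0.22) = 0.587 and 1 − Φ(0.305/0.25) = 1 − Φ(1.22) = 0.111, sum 0.698.

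| SD | Mean gain | Improved ≥ 0.125 | Worsened ≥ 0.125 | Either |
|---|---|---|---|---|
| 0.25 | 0.18 | 58.7% | 11.1% | 69.8% |
| 0.25 | 0 | 30.9% | 30.9% | 61.7% |
| 0.143 | 0.18 | 65.0% | 1.6% | 66.6% |
| 0.143 | 0 | 19.1% | 19.1% | 38.2% |

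Contrast between arms:

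- SD 0.25: 58.7 − 30.9 = 27.8 points with direction; 69.8 − 61.7 = 8.1 points without.
- SD 0.143: 65.0 − 19.1 = 45.9 points with direction; 66.6 − 38.2 = 28.4 points without.

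Using the design difference of 0.2 in place of 0.18, with SD 0.25, the rates are 61.8% vs 30.9% with direction and 71.5% vs 61.7% without. Power for the responder comparison at 25 per arm falls from about 60% to about 11%. Under the literal rise of at least 0.125, the rates are 9.7% vs 30.9%, so the arms rank in reverse.

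**4. Fit with the week 3 rule.**

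A child whose LogMAR rises by 0.125 at week 3 exceeds the 0.1 regression threshold. Under an undirected responder rule the same child would also be a week 3 responder. The two sections must be reconciled on direction.

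**The case against.** The strongest reply is that the sentence is about visual acuity, so the increase may be an increase in acuity, merely sized in LogMAR units. The article does elsewhere put direction in words and size in LogMAR units, as in the pilot results and the week 3 rule. Nor does the sentence define an endpoint: nothing listed counts children who gain 0.025. The objectives call the 0.125 change a response, and losing five letters is not a response. The responder endpoint is secondary and described as supportive, and coding detail is commonly left to the SAP.

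Most of this stands, and it limits the point. A reader might infer that worsening children will be scored as responders. The documents do not support that: the objectives show the intent, so misscoring follows only from literal coding. A reader might also infer that the primary test is compromised, and step 2 shows that it is not.

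The figures also need care. Children who have regressed by 0.1 or more at week 3 are to be withdrawn, and the primary analyses impute nothing, so large losses at weeks 6 and 10 should be rarer than the untruncated model implies. All nine pilot completers improved, and with the pilot mean and SD only 1.6% of the active arm would be misclassified.

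What does not stand is that there is nothing to correct. Deferral to an SAP covers detail left out; it does not cover a direction printed the wrong way round in the outcome definition. The charitable reading has to be supplied by the reader.

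**Conclusion.** The point holds as a should-fix correction of an outcome definition. Read as a score, the improvement sentence runs against the LogMAR scale. The responder rule is undirected in both places, and only the word for response in the objectives shows what is meant.

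If the rule were coded in either direction, the illustrative responder contrast would fall from about 28 to 8 points at SD 0.25, or from about 46 to 28 points at SD 0.143. These sizes assume normal changes, a control arm with no mean change, and no loss of children to the week 3 rule. They apply most directly at week 3, and even there the 0.18 gain is borrowed from pilot patients who had completed treatment.

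It is tempting to rate this as an error that invalidates the primary result. The documents do not support that. The primary analysis is a two-sided comparison of a continuous change, and its p-value, power and sample size are the same whichever way change is signed. What is exposed there is the sign of the estimate and the reading of which arm did better.

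**What to change.** In the outcome definition, and in the SAP before it is finalised:

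1. State that improvement is a decrease in amblyopic-eye LogMAR.
2. Define change as baseline minus follow-up, so that positive is better. This matches the numerator of the article's own proportion-of-change formula.
3. Define a responder, in both the objectives and the secondary endpoints, as an amblyopic-eye improvement of at least 0.125 LogMAR.

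Reporting worsening of at least 0.125 as its own category is optional. The cost is a few sentences. No data collection, sample size or primary test changes. The article reports 21 of 75 patients randomised and an SAP still to be finalised before database lock, so the correction can be made before analysis.

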### Safety assessment

All adverse events will be recorded. They will be categorised according to whether they are device related according to the Figure 2.

**Figure 2 F2:**
[figure not shown]
Classification of adverse effects.

Events which could be considered to be anticipated due to the hypothesised mechanism of action of the treatment include nausea, photosensitive epilepsy, headache, diplopia and reverse amblyopia. None of these events have been observed in previous studies.

### Sample size

Assuming a standard deviation (SD) of 0.25 [8], 25 patients per arm would be required to detect a minimum difference of 0.2 LogMAR units at the 5% significance level (two-sided) with 80% power. Therefore a total of 75 patients would be required.

### Statistical methods

The primary endpoint is considered confirmatory with secondary endpoints considered supportive.

The primary analyses will be performed on the intention-to-treat (ITT) population. Supportive analyses may be performed on a per protocol (PP) population defined prior to code-break.

Except where a patient has been withdrawn from the study or otherwise documented, all missing data will be assumed to be missing completely at random (MCAR). The primary analyses will not use any imputation methods to compensate for missing data.

There will be two primary comparisons: I-BiT™ games *vs.* non-I-BiT™ games and I-BiT™ DVD *vs.* I-BiT™ games. Both these analyses will comprise ANCOVA using baseline visual acuity as a co-variate, where distributional assumptions are met. If these assumptions are not met, a suitable transformation will be applied or a non-parametric method used. There will be no correction for multiplicity.

Summary statistics including mean, median, SD and 95% confidence intervals will be provided, in addition to appropriate graphical displays.

All datasets will be defined in a blinded manner prior to database lock.

Further details of the statistical analyses will be provided in the statistical analysis plan which will be finalised prior to database lock.

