**Methods/design:**

Seventy-five patients aged between 4 and 8 years with a diagnosis of amblyopia will be randomised to one of three treatments with a ratio of 1:1:1 - I-BiT™ game, non-I-BiT™ game, and I-BiT™ DVD. They will be treated for 30 minutes once weekly for 6 weeks. Their visual acuity will be assessed independently at baseline, mid-treatment (week 3), at the end of treatment (week 6) and 4 weeks after completing treatment (week 10). The primary endpoint will be the change in visual acuity from baseline to the end of treatment. Secondary endpoints will be additional visual acuity measures, patient acceptability, compliance and the incidence of adverse events.

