### Randomisation and codebreaking

Subject numbers will be assigned sequentially as each subject enters the study. The subjects will be assigned to a study treatment arm through an independently-developed web-based randomisation system. Randomisation will be performed after eligibility has been checked prior to first treatment, and will be equal and stratified according to whether the patient has had previous treatment for their amblyopia. The research orthoptist will be the only member of the study team who will have knowledge of the randomised treatment.

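### Randomisation is stratified by previous amblyopia treatment, but the primary ANCOVA as stated adjusts only for baseline acuity; standard errors are too wide if previous treatment predicts response

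*Protocol article*

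**What the plan says.** In the protocol article, Randomisation and codebreaking states that allocation "will be equal and stratified according to whether the patient has had previous treatment for their amblyopia". No other stratification factor is named.

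Statistical methods sets out two primary comparisons, I-BiT game against non-I-BiT game and I-BiT DVD against I-BiT game, and gives the model: "Both these analyses will comprise ANCOVA using baseline visual acuity as a co-variate, where distributional assumptions are met". Baseline acuity is the only covariate named. The fallback follows: "If these assumptions are not met, a suitable transformation will be applied or a non-parametric method used". The section calls the primary endpoint confirmatory, applies no multiplicity correction, and leaves further detail to a SAP that is to be final before database lock. That SAP is not at hand.

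Sample size rests on these inputs: "Assuming a standard deviation (SD) of 0.25", enough patients to "detect a minimum difference of 0.2 LogMAR units", "at the 5% significance level (two-sided) with 80% power". The result is 25 per arm and 75 in all.

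**The concern.** Stratified allocation forces the arms to be alike on previous treatment, so the treatment difference varies less from one possible allocation to another than it would under simple randomisation. An analysis that ignores the stratum does not see this. It leaves the between-stratum variance in the residual and reports a standard error that is larger than the true one. Confidence intervals are then too wide, the actual type I error falls below the nominal 5%, and some attainable power is not used.

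The power matters because the design has little to spare: 25 per arm gives almost exactly 80% with no visible allowance for losses.

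A smaller, related matter is that the method for a confirmatory endpoint may change after the distribution is examined. The article names neither the trigger nor the replacement, and it describes the definition of the datasets as blinded but says nothing on the choice of test. A simple rank test would drop the baseline adjustment and would not give an adjusted difference in LogMAR.

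**Working it through.** **Inputs from the article.** Difference 0.2 LogMAR, SD 0.25, two-sided 5%, 80% power, 25 per arm (Sample size); 1:1:1 allocation (Abstract, Methods/design); one stratifier (Randomisation and codebreaking); baseline acuity as the named covariate (Statistical methods).

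**Assumptions, because the article gives no figure.** Strata are 50:50. The SD of 0.25 is taken as the residual SD after baseline adjustment and before stratum adjustment. R² is the share of that residual variance explained by previous treatment. In the simulation, blocks of 6 are used within each stratum.

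**Step 1: the plan's own figure.** n = 2 × 0.25² × (1.960 + 0.842)² / 0.2² = 24.5, so 25 per arm. The standard error is 0.25 × √(2/25) = 0.0707, and power is Φ(0.2/0.0707 − 1.960) = Φ(0.868) = 80.7%. By the noncentral t it is 79.1%. The stated sample size reproduces.

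**Step 2: from a stratum difference to R².** Two equal strata whose mean change differs by d contribute variance d²/4, so R² = (d²/4)/0.25².

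- d = 0.05: 0.000625/0.0625 = 1%
- d = 0.10: 0.0025/0.0625 = 4%
- d = 0.15: 0.005625/0.0625 = 9%
- d = 0.20: 0.01/0.0625 = 16%

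**Step 3: effect of leaving the stratum out.** With the arms balanced on it:

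- Model SE / true SE = 1/√(1−R²)
- Type I error = 2 × [1 − Φ(1.960/√(1−R²))]
- Power, factor omitted = Φ[(0.2/0.0707 − 1.960)/√(1−R²)]
- Power, factor included = Φ[0.2/(0.0707 × √(1−R²)) − 1.960]

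| R² | SE too wide by | Type I error, omitted | Power, omitted | Power, included |
|---|---|---|---|---|
| 0 | 0% | 5.0% | 80.7% | 80.7% |
| 0.04 | 2.1% | 4.5% | 81.2% | 82.3% |
| 0.09 | 4.8% | 4.0% | 81.9% | 84.3% |
| 0.10 | 5.4% | 3.9% | 82.0% | 84.7% |
| 0.16 | 9.1% | 3.2% | 82.8% | 87.0% |
| 0.20 | 11.8% | 2.8% | 83.4% | 88.5% |

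As one line worked through, at R² = 0.09, √0.91 = 0.954 and 1/0.954 = 1.048. Then 1.960 × 1.048 = 2.055, which gives a two-sided tail of 4.0%.

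**Step 4: check by simulation** (6,000 three-arm trials of 75 per setting, game against control, ANCOVA on baseline with and without the stratum).

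- R² = 0: type I error 5.0% omitted, 4.9% included.
- R² = 0.10: model SE 0.071 against a true 0.068; type I error 3.6% omitted, 4.4% included; power 79.5% omitted, 82.7% included.
- R² = 0.20: model SE 0.071 against 0.064; type I error 3.0% omitted, 4.9% included; power 80.8% omitted, 86.8% included.

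Monte Carlo error is about 0.3 points at 5%. The gain is 3 to 6 points by simulation, and 2.4 to 5.1 points by the formula for R² of 0.09 to 0.20.

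**Step 5: the switching clause**, simulated at R² = 0. A fixed rule (Shapiro-Wilk at 5%, then Mann-Whitney or rank ANCOVA) gives type I error of 5.1% with normal errors and 5.2% to 5.5% with skewed errors. Taking the smallest p-value of three tests gives 6.6% and 8.0%.

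**The case against.** The article is a condensed account, it defers detail to a SAP that is not at hand, and its wording does not say that baseline acuity is the sole covariate. The SAP may therefore already include the stratum. This deserves weight, but the covariate for the primary model is stated here and the stratifier is not, so asking for it amends a stated analysis and does not merely fill in an omitted detail.

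The loss is also hypothetical. A stratum difference of 0.15 or 0.20 LogMAR is large: the pilot's whole mean improvement was 0.18, so these are 83% and 111% of it, and 0.20 equals the target treatment difference. At a difference of 0.05 the standard error is only about 0.5% too wide. This stands, and the size has to be given as a range that starts at zero.

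A reader might infer that the omission biases the comparison, inflates false positives or leaves the trial short of its planned power. None of these follows. The estimate is unbiased, type I error stays at or below 5%, and power with the factor omitted does not fall below the design value. What is forgone is a possible gain.

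A reader might also infer that the fallback clause leaves the primary test with no controlled error rate. The text ties the switch to failed assumptions and does not allow a choice by smallest p-value, and the SAP may fix the rule. A fixed rule costs almost nothing (step 5). Nor would a switch disturb the 0.125 LogMAR threshold, which belongs to a secondary responder endpoint. LogMAR summaries with confidence intervals are planned in any case.

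**Conclusion.** The point holds in conditional form. The article stratifies on previous treatment and states a primary model that does not name it. If previous treatment predicts change beyond baseline acuity, the standard errors are too wide and the test is conservative. The excess is 0% to about 5% for R² of 0 to 0.10, and 9% to 12% for R² of 0.16 to 0.20. These sizes rest on the assumed 50:50 strata and on reading the SD of 0.25 as the residual SD. The direction does not depend on the exact values. This is an inexpensive improvement in precision and not a threat to validity.

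The open switching rule is a secondary point and not a demonstrated error. It becomes a problem only if the choice of method is still open once unblinded results are visible.

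**What to change.** Add previous amblyopia treatment (yes/no) as a factor to both primary ANCOVAs, alongside baseline acuity. Two pairwise models are valid; taking both contrasts from one three-arm model is a matter of preference. The cost is a line of wording and one degree of freedom per model, and the factor is already recorded for randomisation. The sample size does not change.

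Secondarily, keep this adjusted ANCOVA on the LogMAR scale as the primary analysis whatever the residuals show, and name one rank-based or permutation analysis as a sensitivity analysis. If a switch is to be retained, the SAP should state, before unblinding, the check, its threshold and the single replacement method. Either option costs wording only.

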### Monitoring

No data monitoring committee will be appointed for this study due to the expected low incidence of adverse events. Routine data monitoring will be performed in accordance with the sponsor’s standard operating procedures.

### Ethical considerations

The study has received approval from both the Research Ethics Committee and Medicines and Health Regulatory Authority (MHRA) and will be conducted in accordance with the Declaration of Helsinki, ICH GCP and ISO14155.

## Discussion

This is the first randomised controlled study using the I-BiT™ system. It aims to determine whether the improvements in visual acuity observed in previous, uncontrolled studies of I-BiT™ technology are maintained under strict clinical trial conditions. It also aims to determine whether there is a difference between playing games and watching DVDs using I-BiT™ technology, and whether there is a difference between playing games using and not using the I-BiT™ technology and therefore identify which is the optimal treatment to develop.

Compliance is a huge issue with conventional patching treatment which impacts on the efficacy of the treatment. Therefore this study also aims to determine the compliance of patients undergoing each of the treatments.

The study also aims to determine whether there are any adverse effects which could be related to I-BiT™. It has been hypothesised that there is a theoretical risk of adverse events such as nausea, photosensitive epilepsy, headache, diplopia and reverse amblyopia. However, none of these events have been observed in previous studies.

It has not been possible to fully blind the study. However, the masking procedures ensure that clinical assessments are made in a blinded manner and therefore should not be subject to bias. The treating orthoptist will have no access to assessment results either through the database or through medical notes and indeed controls are in place to ensure that the treating orthoptist cannot treat these patients after they complete the study and thereby gain access to their resultant visual acuity measurement.

This study looks specifically at patients between the ages of 4 and 8 years. Cleary *et al.*[10] found improvements in older children in a pilot study with an I-BiT™ prototype system. Therefore it is possible that improvements could be gained in patients older than 8 years with the current I-BiT™ system. However, there are no plans formally assess this at present, the priority being to develop an optimal treatment regimen for children.

The results of this study will inform further development. It will be necessary to determine an optimal treatment regimen which may involve more frequent visits or a larger number of treatments in order to provide a long-term effect. It will also be necessary to follow-up patients in the longer term to ensure maintenance of beneficial effects.

If I-BiT™ is shown to be an effective treatment for amblyopia there is great potential for developing this treatment in a number of settings. While making available in hospital orthoptic clinics, there is also the potential that it could be used in high street opticians throughout Europe and even the potential to develop a home-based treatment regimen. There is therefore the opportunity to make improvements in both vision and quality of life for children, but to also decrease treatment costs.

